#### Intervention description {11a}

##### Face-to-face (FtF) circuit protocol

Participants allocated to this group will attend all of their exercise sessions supervised by a trained physical therapist in the Federal University of São Carlos (UFSCar).

The exercise protocol will be performed in a group of up to 5 participants, three times a week, for 14 weeks, totaling 42 sessions [7]. Each session will consist of 5 min of warm-up (stationary bike or walk), circuit protocol, and 5 min of stretching exercises (cool down). Immediately after the warm-up, participants will begin the circuit protocol consisting of exercises for the upper limbs, lower limbs, trunk, and global exercises.

Participants will be instructed to perform each exercise as fast as possible, with the maximum number of repetitions during the time set for the training phase (light, moderate, or intense), in order to ensure the aerobic component [7]. After the first exercise, the participant should move to another station, following a specific order and allowing different muscle groups to alternate between rest and work, favoring recovery and minimizing the risk of muscle fatigue [7].

During the first week of exercise, participants will be familiarized with the equipment and exercises that will be performed during the protocol, performing stratified light exercises, where each exercise should be performed for only 10 s [7]. In the second, third and fifth weeks of training, participants will also perform exercises stratified as light, but each exercise will last 20 s. Moderate exercises will be performed in the sixth, eighth, and ninth weeks, lasting 30 s each. Intense exercises will be performed in the eleventh, twelfth, and fourteenth weeks, lasting 40 s each. The fourth, seventh, tenth, and thirteenth weeks will be considered as regenerative weeks, during which light exercises will be performed for a shorter time (10 s). For all intensities, a maximum transition interval of 30 s between stations will be implemented [7].

The exercises that compound each of the circuit training phases, as well as the execution time are presented in Additional file 1.

##### Telerehabilitation (TR) circuit protocol

Participants allocated to the TR group will be invited to attend the Department of Physical Therapy at UFSCar after randomization and before starting the intervention. This visit will be held individually so that the participant has full attention from the physical therapist to clarify questions, possible adaptations regarding the execution of exercises at home, as well as signs and symptoms to interrupt the session. In addition, during this visit, participants will receive a DVD with recordings of the circuit exercise sessions, the material needed to perform all the exercises, and a diary to record the days that they will perform the exercises. The materials provided to the participants are the same used in the FtF group and include a pair of 0.5-kg dumbbell, a pair of 1.0-kg dumbbell, a light elastic band, a hard-elastic band, a small ball, a 0.5-kg ankle weight, and a 1.0-kg ankle weight.

The TR group exercises will follow the same model proposed for the FtF group, following the same progression, execution time, and rest time (Additional file 1). However, these participants will perform the exercise sessions remotely.

Participants from this group will be instructed to perform the exercises scheduled for this week following the instructions given via DVD, website (http://exercicio-joelho.trekeducation.org), *YouTube* channel (http://bit.ly/telereabufscar), and/or videos via *WhatsApp*. The exercises should be performed three times weekly, preferably on non-consecutive days. Each session will consist of 5-min warm-up (light walking, steady walking), circuit exercises, and cool-down (5-min stretching), identical to the FtF group.

The TR group will also receive periodic phone calls from a single previously trained researcher/physical therapist. The phone calls will take place in weeks 2, 3, 4, 6, 8, 11, and 14; they will be recorded and will last approximately 20 min. In addition, it should be noted that phone calls will be made at participant’s preferred timed and will be motivating and instructive; however, participants will not be informed when calls will be performed. During these phone calls, a semi-structured interview will be performed, as proposed by Hinman et al. [32]. Table 1 presents the semi-structured interview guide. In addition, during these calls, it will be possible to detect possible difficulties with carrying out the exercises, as well as monitor the progress in subsequent calls, assessing the ability to perform the exercises, changes in symptoms, and functional capacity.

**Table 1 Tab1:** Semi-structured interview guide

**Questions**	
1. How was your week?	
2. How are you feeling?	
3. Are you having difficulty performing the exercises?	
4. How often have you been doing the exercises and at what time?	
5. Is any family member doing the exercises with you?	
6. Is there something in your routine that you could modify to be able to perform the exercises?	
7. Do you think exercise is beneficial to your health?	

#### Criteria for discontinuing or modifying allocated interventions {11b}

Participants are free to withdraw from the study at any time and for any reason without penalty. The participant data that have been collected up to that moment will be included in the analysis.

#### Strategies to improve adherence to interventions {11c}

Adherence reminders will take place during the phone calls to the TR group, and during the face-to-face sessions to the FtF group. The researcher/physical therapist will provide support by increasing participants’ knowledge and understanding of knee OA, such as the causes of pain and the benefits of exercise. This will provide strategies for stimulating activity and dealing with pain during exercise, providing realistic expectations of likely outcomes, reaffirming that pain does not need to be feared and helping the participant to build confidence in their ability to perform exercises.

#### Relevant concomitant care permitted or prohibited during the trial {11d}

Permitted concomitant care comprises all drug prescriptions for medical conditions that do not meet the exclusion criteria of the present study. The prohibited care includes the uptake of new physical therapeutic measures.

### Provisions for post-trial care {30}

Trial center insurance will compensate for those who suffer harm from trial participation.

### Outcomes {12}

Figure 1 summarizes the schedule of enrolment, interventions and assessments for this study protocol according to SPIRIT recommendations [33].

**Fig. 1 Fig1:**
[figure not shown]
Schedule protocol. *Abbreviations*: FtF, face-to-face; TR, telerehabilitation; VAS, Visual Analog Scale; WOMAC, Western Ontario and McMaster Universities; CT, computed tomography; DXA, dual energy X-ray absorptiometry; US, ultrasound; BMI, body mass index

#### Primary outcomes measurement

Pain and disability are the primary outcomes of this study protocol and the main symptoms that drive individuals with knee OA seek physical therapy care. In addition, assessing both of these symptoms are strongly recommended as outcomes of change in clinical trials with individuals with knee OA [34]. The primary end-point is 14 weeks and the secondary end-point is 26 weeks.

#### Pain Intensity

Pain intensity will be measured using Visual Analog Scale (VAS). This is a reliable measure of pain [35] consisting of a 100-mm line in which participants must mark between the left side (0, representing “no pain”) and 100 (representing “the worst pain imaginable”). This measure will be self-reported on a paper form.

#### Physical function subscale of the Western Ontario and McMaster universities osteoarthritis index (WOMAC)

To assess physical function, the Western Ontario and McMaster Universities (WOMAC) questionnaire will be used, a self-administered instrument that addresses the impact and restrictions on quality of life, specifically for patients with lower limb OA [36]. The questionnaire has been translated into Portuguese and validated [37], consisting of 24 questions divided into three domains: pain, stiffness, and physical function. The physical function subscale contains 17 questions, and the score is made using a Likert scale, whereby each question is scored between “no dysfunction” (score = 0) to “extreme dysfunction” (score = 4). Total score ranges from 0 to 68, with higher scores indicating worse function. Self-reported answers will be registered on a paper form.

#### Secondary outcomes measurement

All secondary outcomes will be also calculated using data measured at baseline, 14 weeks, and 26 weeks. Only adherence, acceptability, and treatment perspective will be measured at 14 weeks and 26 weeks.

#### Physical function—performance-based tests

The functional performance tests selected for this study follow the recommendations by OARSI (2013) [38]. All tests will be conducted by a single blinded evaluator on baseline and both end-points.

##### 40 m Fast-paced Walk Test

Participants will be instructed to walk as fast as possible without running for a distance of 10 m, returning to the starting point and repeating the walk for a total distance of 40 m. The test will be timed and the speed in meters/second (m/s) will be used for analysis [38, 39].

##### 30-second Chair Stand Test

From the sitting position, with feet flat on the floor and arms crossed over the chest, the participant should stand up completely from the chair and then sit down as quickly as possible for 30 s. The total number of repetitions (standing up and sitting represents one repetition) performed will be recorded [38, 40].

##### Stair climb test

The test will consist of ascending and descending a flight of 12 steps 16 cm high each. Participants should start the test standing on a line and, at the command to start, must climb to the top of the steps and immediately turn and descend as quickly as possible safely. The total test duration will be timed (in seconds); longer times indicate more impaired physical function [38, 40].

#### Knee extensors strength

The maximal isometric torque peak of the knee extensors will be measured using an isokinetic dynamometer (Multi-Joint System 3, Biodex Medical System, New York, USA) with a sampling frequency of 100 Hz by a single blinded evaluator. Knee extensors have been chosen as quadriceps weakness has been widely associated with knee OA [41].

The participant will be positioned on the equipment chair, with the knees flexed at 90^o^ and stabilized by non-elastic bands on the thorax, waist, and thigh of the limb to be tested. The dynamometer’s rotation axis will be aligned with the lateral femoral epicondyle and the movable arm fixed 5 cm above the medial malleolus. In addition, participants will be instructed to keep their arms crossed in front of their chest during contractions. Before performing the test and after receiving instructions, the participant must perform 3 submaximal isometric contractions to become familiar with the test procedure. After familiarization, the participant will be instructed to rest for 2 min.

For isometric extensor torque evaluation, the knee will be positioned at the 60° of flexion angle. The test will consist of 3 maximum contractions held for 3 s each, with a 1-min rest between contractions. Standard verbal encouragement will be given during the test [41–43].

The isometric peak torque will be calculated as the average of the three contractions [44]. The isometric mean peak will be normalized by body mass (kg) (mean isometric peak torque/body mass × 100) and used for statistical analysis.

#### Thigh composition

The CT will be performed to assess thigh composition (intermuscular fat, subcutaneous fat, muscle mass and mean muscle attenuation). The images will be obtained through a Multislice Tomograph (Brilliance CT 16-slice, Phillips), located at UH-UFSCar, by an experienced radiologist.

For image acquisition, the criteria according to Eastwood et al. [45] will be followed, comprising the following parameters: helical mode, 120 KV, 150 mAs, slice thickness = 5 mm, and 50 cm field of view. The suggested protocol will provide a mid-thigh image of the most affected limb. To quantify the thigh tissues, the images will be obtained at the midpoint between the greater trochanter and the femoral intercondylar fossa. During the exam, the participant will remain in the supine position, with their hands resting on the head and arms flexed at 90° for approximately 3 min.

Thigh composition analyses will be performed manually using the ITK-SNAP software (version 3.6) [10] by a single evaluator blinded to the interventions group. The 2 middle slices will be selected for segmentation, representing 10 mm of the area of interest. Thus, the area of interest of each slice will be selected by scanning according to the attenuation rates for quantification of adipose tissue present in cm^2^. In addition, a manual line will also be performed separating the bony part from the soft tissues and then the adipose tissue present within the bone area will be subtracted from the area obtained by measuring intermuscular and subcutaneous adipose tissue.

Skeletal muscle and adipose tissue areas will be calculated by the attenuation value range for skeletal muscle tissue (0 to 100 Hounsfield) and adipose tissue (−190 to −30 Hounsfield) [46, 47]. The mean muscle attenuation will be calculated by the average of the Hounsfield values obtained in the muscle fascia area. The intra-rater reliability performed at 1-week interval was ICC = 0.97 and interrater reliability was ICC = 0.99 (*n* = 20).

#### Body composition

For body composition analysis, the reference standard will be the Dual Energy X-ray absorptiometry (DXA) device (Discovery A, Hologic), which uses the three-compartment model (lean body mass, adipose tissue, and bone mineral density). This technique estimates the body composition in the whole and by body segment. Scanning will be performed according to the manufacturer’s recommendations. Thus, the operator should check that no metal objects remain in the scanning area [48]. Participants will be asked to attend in a fasted state (at least 4 h) and not to perform any physical activity within 24 h prior to the exam [7]. The participant will be placed in the supine position and should remain un-moving during the exam. The device software will automatically define areas of regional body estimates (left and right arms, legs and trunk) [48]. For this study, it was defined that the segment areas and total body composition will be used for analysis.

#### Muscle architecture

The pennation angle (PA), muscle thickness (MT), and fascicle length (FL) of the vastus lateralis muscle will be obtained using an ultrasound device (US) (Acuson X300 PE, Siemens) and linear transducer (4–11.4 MHz). The same previously trained evaluator, blinded to intervention groups, will obtain all images. The vastus lateralis was the chosen muscle for analysis due to the simple fascicle alignment when compared to the other quadriceps muscles [49].

For image acquisition, the participants will be positioned supine with legs extended and relaxed muscles [50]. Three vastus lateralis images will be collected at the midpoint of the thigh, measured as the midpoint between the greater trochanter and the lateral femoral epicondyle [49]. Water-soluble gel will be applied between the transducer and the skin to aid in acoustical coupling and to prevent pressure muscle deformation. The transducer will be oriented parallel to the muscle fascicles during the image acquisition.

A second investigator, also blinded to interventions group, will manually review all obtained images using the ImageJ software (National Institutes of Health, USA). PA will be defined as the insertion angle of the fascicle in the deep aponeurosis [51]. MT will be defined as the distance between deep and superficial aponeurosis [44, 49]. FL will be defined as the distance between the origin of the fascicle in the superficial aponeurosis and the insertion of the same fascicle in the deep aponeurosis [51–53]. The average of the three MT, PA, and FL measurements will be used for analyses.

The intra-rater reliability performed at 1-week interval was ICC = 0.97 (*n* = 10).

#### Pain catastrophizing

The Pain Catastrophizing Scale (PCS) is a valid, reliable, and self-applicable 13-item scale that describes thoughts and feelings that people may experience when they experience pain [54]. Items are evaluated using a 5-point Likert scale, ranging from 0 to 4. The total score is calculated by the sum of the scores for all items (total score, 0–52). Higher scores indicate greater catastrophic thoughts about pain. A score greater than 30 represents a clinically relevant level of catastrophism [54].

#### Adherence, acceptability, and treatment perspective

Adherence/acceptability to TR, as proposed by Hinman et al. [32] will be assessed by the number of calls received from the lead investigator, as well as the number of sessions per week the participant performed, which should be self-reported during phone calls. The FtF will be evaluated by the number of sessions that the participant attended. In addition, for the same purpose, questions will be asked such as “Do you agree with the proposed exercise plan?” and “Did you perform the exercise program?” Where 0 refers to “strongly disagree” and 10 “strongly agree”. The participants will also qualitatively evaluate the expectation with the result of the exercise protocol, where the scale may vary from “no effect” to “complete recovery” [32]. These outcomes will be self-reported on a paper form only during end-points (14 weeks and 26 weeks).

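### The adherence comparison is not like for like: FtF is counted from attendance at 42 scheduled sessions, TR from self-report at seven phone calls with no stated recall window

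*Protocol article*

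**What the plan says.** The Objectives section of the protocol article lists adherence among the secondary comparisons. The section on adherence, acceptability and treatment perspective gives each arm its own source:

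- **FtF:** "The FtF will be evaluated by the number of sessions that the participant attended". The FtF intervention section gives the schedule: "three times a week, for 14 weeks, totaling 42 sessions".
- **TR:** the number of calls received, together with "the number of sessions per week the participant performed, which should be self-reported during phone calls". The TR intervention section sets the calls: "The phone calls will take place in weeks 2, 3, 4, 6, 8, 11, and 14".

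The call guide (Table 1) has one question on frequency: "How often have you been doing the exercises and at what time". It names no period.

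Before starting, TR participants are also given "a diary to record the days that they will perform the exercises". Neither the adherence section nor the data-collection plan names this diary as a source for the session count.

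The calls are part of the intervention. The TR section describes them as motivating and instructive, and the section on strategies to improve adherence places the TR adherence reminders in them.

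**The concern.** The two arms differ in source, in coverage and in who collects the information. FtF adherence is observed at every session. TR adherence is a verbal report to the physical therapist who delivers the support, given during the support contact, at seven points whose reference period is not defined. A day-by-day record exists in the TR package but has no stated role. Calls received are initiated by the research side and have no FtF counterpart, so listing them under adherence/acceptability mixes delivery of the package with what the participant did.

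This matters because the Abstract makes the benefit of remote rehabilitation depend on adherence, and the only planned analysis is by intention to treat. If the arms come out similar on pain and function, readers will look to adherence to judge whether they also exercised similarly. Figures built in two different ways cannot answer that.

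**Working it through.** **Inputs.** FtF schedule: 3 sessions a week for 14 weeks (FtF section). Call weeks: 2, 3, 4, 6, 8, 11 and 14 (TR section). TR frequency: "The exercises should be performed three times weekly, preferably on non-consecutive days" (TR section). Training phase by week: FtF section, with the same progression in TR.

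**1. The plan's own figure.** 3 × 14 = 42 sessions. This reproduces.

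**2. What the calls cover.** The documents allow two readings.

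- *Each call reports its own week.* Coverage is 7/14 = 50% of weeks, or 7 × 3 = 21 of 42 scheduled sessions. Weeks 1, 5, 7, 9, 10, 12 and 13 are not covered.
- *Each call reports the time since the previous one.* The intervals are 2, 1, 1, 2, 2, 3 and 3 weeks, which sum to 14. All weeks are covered, but by recall over as much as 3 weeks.

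**3. Are the call weeks representative?** By training phase:

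| Phase | Weeks | Weeks with a call |
|---|---|---|
| Familiarisation | 1 | 0 of 1 |
| Light | 2, 3, 5 | 2 of 3 |
| Moderate | 6, 8, 9 | 2 of 3 |
| Intense | 11, 12, 14 | 2 of 3 |
| Regenerative | 4, 7, 10, 13 | 1 of 4 |

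On the first reading, the familiarisation week is missed and regenerative weeks are under-represented.

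**4. Size of the error on the first reading.** Let p_c be completion in call weeks and p_o completion in the other weeks, with three sessions scheduled every week and accurate reporting.

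- Reported: p_c
- True: (7 p_c + 7 p_o)/14 = (p_c + p_o)/2
- Error: p_c − (p_c + p_o)/2 = (p_c − p_o)/2

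The documents give no completion rates, so these differences are assumptions:

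| p_c − p_o (points) | Error in TR adherence (points) |
|---|---|
| +30 | +15 |
| +20 | +10 |
| +10 | +5 |
| 0 | 0 |
| −10 | −5 |
| −20 | −10 |
| −30 | −15 |

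For example, 80% in call weeks and 60% in the others gives a report of 80% against a true 70%. Reversing the two gives 60% against 70%.

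On the second reading this term vanishes. What remains is recall error, which cannot be quantified from the documents.

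**5. Ceiling.** The Abstract sets three sessions a week as a minimum for TR, whereas the TR section says three. Under the Abstract's wording a TR count can exceed 42, while FtF attendance cannot. These passages must be reconciled before a common denominator is used.

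**The case against.** The strongest reply is that the call schedule says when calls happen, not what period each report covers. The guide question reads naturally as the time up to the call, so all 14 weeks may be covered. That stands. A reader might infer that half the programme goes unmeasured; the documents do not establish it.

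A reader might also infer that TR adherence will be overstated, because the sampled weeks are the prompted ones. The documents do not support a direction. Participants are not told when calls will come, so a call cannot prompt sessions done before it. The weeks without a call include the familiarisation week and three of the four regenerative weeks, when exercise is light and short and completion could well be higher.

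A third inference is that the adherence section contradicts itself, since it ends by confining these outcomes to a paper form at 14 and 26 weeks. That sentence follows the 0–10 agreement items and the expectation scale and most naturally refers to them; FtF attendance is plainly not self-reported on a form. The wording is loose, no more.

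Other mitigation is real. The Discussion discloses that TR participation is self-reported and cannot be verified. The 0–10 items carry no restriction by arm and so give one common measure. Nothing says that the diary is not collected, and an article may leave its handling to a fuller document.

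What remains is that the section does more than stay silent: it states a source for each arm, the sources differ, and the one named for TR is phone report rather than the diary. The Discussion mentions neither the coverage of the calls nor the diary, and the 0–10 items do not repair the session count.

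**Conclusion.** The point holds for the session-count comparison. As defined, FtF rests on observed attendance over 42 sessions. TR rests on verbal report at seven motivational calls, covering either 7 of 14 weeks or recall intervals of 1 to 3 weeks. Calls received enter under adherence/acceptability in TR only.

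The size and direction of any bias are unknown. The half-the-difference result applies only if each call captures its own week and reports are accurate; the differences tabulated are illustrations, not estimates.

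The consequence is confined to a secondary outcome. Adherence enters no stated primary analysis, and the non-inferiority conclusion and sample size are untouched. The change is worth making because it is cheap and the better record is already part of the TR package.

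**What to change.** - Define adherence in both arms as sessions completed out of the 42 scheduled, once the two statements of TR frequency have been reconciled.
- Take the count from the attendance log in FtF and from the diary over all 14 weeks in TR.
- Have the diary collected by someone other than the blinded assessor, since only TR participants hold one.
- Use phone reports as a check, and as the fallback where no diary was kept. State the recall window for the frequency question.
- Report calls received separately, as delivery of the TR intervention.

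**Cost:** diary data entry and a change in outcome wording, with no extra visits. The TR figure remains self-reported, so the limitation in the Discussion still applies. According to the trial status section the first two blocks are complete, which is 20 + 40 = 60 of the 100 participants. Whether their diaries were returned is not stated. The number of TR participants with a usable diary, and the number counted from phone report instead, should be reported.

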**Methods:**

This study presents a single-blinded protocol for a non-inferiority randomized controlled trial. One hundred participants diagnosed with knee OA (grades II and III Kellgren and Lawrence system), aged 40 years or more, and BMI < 30 kg/m^2^ will be randomly divided into two groups: telerehabilitation (TR) and face-to-face (FtF) circuit training. The FtF group will perform a 14-week periodized circuit training protocol supervised by a physical therapist, 3 times a week. The TR group will perform the same exercise protocol at home, at least 3 times a week. In addition, the TR group will be able to follow the execution and orientations of the exercises by DVD, a website, and online file sharing tools, and they will receive periodic phone calls in order to motivate, clarify, and inform some aspects of knee OA. The primary outcomes are changes in self-reported pain intensity (visual analog scale (VAS)) and physical function (Western Ontario and McMaster Universities Osteoarthritis Index (WOMAC)), with a primary end-point of 14 weeks and a secondary end-point of 26 weeks. Secondary outcomes include changes in other clinical outcomes, in morphological characteristics, adherence, acceptability, and treatment perspective.

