### Methods in analysis to handle protocol non-adherence and any statistical methods to handle missing data {20c}

The primary and secondary outcomes will be assessed using an intention-to-treat-analysis. Multiple imputation method will be used to impute missing data.

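### The multiple-imputation rule, which has no exceptions, also covers adherence, so telerehabilitation participants who stop exercising and stop answering calls would be credited with sessions, while face-to-face absences lower the count

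*Protocol article*

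**What the plan says.** Adherence is a secondary outcome. The abstract states "Secondary outcomes include changes in other clinical outcomes, in morphological characteristics, adherence, acceptability, and treatment perspective", the Objectives section names adherence among the secondary aims, and Secondary outcomes measurement gives its timing: "Only adherence, acceptability, and treatment perspective will be measured at 14 weeks and 26 weeks".

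The section on non-adherence and missing data {20c} sets one rule for all of these: "The primary and secondary outcomes will be assessed using an intention-to-treat-analysis. Multiple imputation method will be used to impute missing data". Statistical methods {20a} adds that the SPSS multiple-imputation function will be used and that all randomized participants are included. Neither section exempts any outcome.

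The section on adherence, acceptability and treatment perspective uses a different source in each arm. For FtF: "The FtF will be evaluated by the number of sessions that the participant attended". For TR, it uses the number of calls received and "the number of sessions per week the participant performed, which should be self-reported during phone calls". According to the TR circuit protocol section, the calls fall in weeks 2, 3, 4, 6, 8, 11 and 14, at a time of day the participant prefers, although "participants will not be informed when calls will be performed".

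**The concern.** The same behaviour is recorded differently in the two arms. An FtF participant who gives up is seen not to attend, and the count falls. A TR participant who gives up and stops picking up the phone supplies no session count, and the stated rule then treats that as a missing value to be imputed. The likely reason for silence is the very thing being measured, so missingness would depend on the unseen value. Imputation under missing at random would borrow from TR participants who kept answering.

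At stake is the between-arm adherence comparison. The abstract's background says that the benefit of remote rehabilitation depends on adherence, so readers will look at this comparison when they interpret the main result. Equal behaviour in the two arms could appear as better adherence in TR.

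**Working it through.** **Inputs from the protocol article.** Planned sessions: 3 per week × 14 weeks = 42, which agrees with the stated 42. TR calls: 7, in weeks 2, 3, 4, 6, 8, 11 and 14. Loss to follow-up allowed for in the sample size: 18%, used below only as a middle value.

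**Assumptions, not in the documents.** Both arms behave identically. Everyone does r = 2.4 sessions per week (80% of 3) while active. A share q stops both exercising and answering after week s. Range: q = 10%, 18%, 30%; s = 4 to 10.

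**Formulas.**
- True mean, which is also the FtF count: r × [(1 − q) × 14 + q × s].
- TR mean if the silent weeks are filled from answerers: r × 14 = 2.4 × 14 = 33.6 sessions (80.0% of 42).
- Bias: q × r × (14 − s).

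| q | s | True / FtF sessions | TR imputed | Bias, sessions | Bias, points of 42 |
|---|---|---|---|---|---|
| 10% | 10 | 32.6 | 33.6 | 1.0 | 2.3 |
| 10% | 4 | 31.2 | 33.6 | 2.4 | 5.7 |
| 18% | 10 | 31.9 | 33.6 | 1.7 | 4.1 |
| 18% | 4 | 29.3 | 33.6 | 4.3 | 10.3 |
| 30% | 10 | 30.7 | 33.6 | 2.9 | 6.9 |
| 30% | 4 | 26.4 | 33.6 | 7.2 | 17.1 |

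For example, with q = 18% and s = 4: 0.18 × 2.4 × 10 = 4.3 sessions, and 4.3 / 42 = 10.3 points.

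**Simulation check.** There were 50 participants per arm, 5 imputations and 400 replicates. Each missing call-week report was imputed by regression on the mean of the participant's earlier reports.
- q = 18%, s = 4: FtF 29.2, TR true 29.2, TR after imputation 33.5.
- q = 30%, s = 4: FtF 26.3, TR true 26.2, TR after imputation 33.5.

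Earlier reports alone did not remove the bias here, because the simulated stoppers looked like everyone else until they stopped.

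**Why silence cannot simply be scored as zero out of 42.** If each call covers its own week, a TR participant who answers every call and does every session can report at most 7 × 3 = 21 sessions, and 21 / 42 = 50%. The comparison has to be limited to the call weeks.

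**The proposed comparison under the same assumptions, q = 18%.**
- s = 4: stoppers answer 3 of 7 calls. Both arms show 2.4 × (0.82 × 7 + 0.18 × 3) = 15.1 of 21 (71.8%).
- s = 10: stoppers answer 5 of 7 calls. Both arms show 2.4 × (0.82 × 7 + 0.18 × 5) = 15.9 of 21 (75.9%).
- Reporters-only TR figure in both cases: 2.4 × 7 = 16.8 of 21 (80.0%).

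**The case against.** The strongest reply is that the harmful step is inferred. The article does not say that an unanswered call yields a missing value, does not give the imputation model, and says a full statistical plan will be finalised if appropriate. That FtF absences count as zero also follows only from counting attended sessions. This stands as a limit on certainty. It does not remove the point, because the article states a rule without exceptions, and that rule, followed literally, mishandles this outcome.

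The plan also has other signals of disengagement. Calls received is itself a TR measure and would fall. Both arms rate at 14 and 26 weeks whether they performed the programme, all randomized participants are invited to those visits, and TR participants keep a diary. These would show some of the silence, and could reduce the bias if they entered the imputation model. However, calls received has no FtF counterpart, and the diary is not named as the source of the session count. The limitation acknowledged in the Discussion concerns whether reports are true, not what happens when there is no report.

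A reader might infer three stronger things that the documents do not support:
- **That imputation can never recover the missing sessions.** Seven calls mean that most stoppers would have earlier reports, and the model is not specified.
- **A larger bias, from treating non-reporters as silent for all 14 weeks.** With 18% silent, 80% adherence in reporters and 20% in the silent, the true value is 0.82 × 80 + 0.18 × 20 = 69.2%, a bias of 10.8 points; wider assumptions reach 24 points. That calculation discards every earlier call report, and its rates are assumed.
- **That the rule also hides participants unable to complete a performance test.** The stair climb section says "The total test duration will be timed (in seconds); longer times indicate more impaired physical function", but nothing says how an uncompleted test is recorded, so this remains speculation.

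**Conclusion.** The point holds for session adherence only. Under ordinary missing-at-random imputation, the stated rule biases the secondary adherence comparison towards TR if those who stop answering have also stopped exercising. The size is illustrative: about 2 to 17 percentage points (1.0 to 7.2 of 42 sessions) for 10% to 30% stopping after week 4 to week 10. It is smaller if the imputation model uses calls received, or earlier reports that decline before the silence, and zero if non-answerers exercise like answerers. The 18% is the sample-size loss allowance, not a rate of unanswered calls.

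A reader might infer that the non-inferiority conclusion is compromised. It is not: the pain and function tests and the sample size do not use the adherence count.

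**What to change.** In Statistical methods {20a} and in section {20c}, state that session adherence is exempt from multiple imputation. Then specify:
- Compare the arms on the same seven weeks (2, 3, 4, 6, 8, 11 and 14; up to 21 sessions), using FtF attendance in those weeks and the sessions TR participants report for them.
- In the main summary, count a TR call week with no answered call as no sessions.
- Beside it, show the reporters-only TR figure as the upper bound, together with the number of calls answered.

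The cost is a short paragraph of analysis wording. No new data are needed, provided that FtF attendance and answered calls are held by week, which the article implies but does not state. The Trial status section says the final 40 participants had not started, so the wording can be settled before the final analysis. The downside is that the main figure may understate TR adherence for someone who exercised but missed a call, which is why both figures are shown. No performance test needs rescoring.
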